## Statistical methods

### Statistical methods for primary and secondary outcomes {20a}

Data from all patients included in this study will be included in the final analysis, following the modified intention to treat (mITT) principle. Data may be excluded from the analysis if an automated VF assessment was not obtained and/or VF parameter values are not reliable.

The number of patients presenting a major deviation to the protocol will be listed, and a sensitivity analysis on the per protocol population will be conducted. The major deviations will be reviewed by the trial’s data and safety monitoring board (DSMB).

The quantitative variables will be presented as means and standard deviations. The qualitative variables will be presented as numbers and percentages. Statistical analysis will be performed using STATA® Software Version 14.2 or higher (Stata Corporation [name]). Data normality will be evaluated graphically and tested using the Shapiro-Wilk test. The statistical tests will be interpreted considering a two-sided *p*-value < 0.05 as significant.

For the *primary endpoint analysis*, the progression in the MD (in decibels) of the VF between baseline (inclusion visit, D1) and the 3-month visit (M3) measured using automated perimetry, i.e. delta M3 – D1, will be compared between the two groups using a linear mixed effects model, with the group as a fixed factor. The study centre will be included in the model as a random effect, and the MD at baseline will be included as a covariate in the model.

A second model of the same type will be built, adjusted on the presence of OSAS and on other baseline parameters that potentially differ between the two groups (here the *Y* variable will be the difference in RNFL: M3 – D1). The quantitative variables will be log-transformed if their distribution is not normal, so as to satisfy the conditions required to apply linear models.

For the *secondary endpoint analyses*, the same type of analysis as that used for the primary endpoint will be used for VA. Other comparisons between the two groups will be made using the Student *t* test or the Mann–Whitney *U* test (depending on the normality of the data distribution) for quantitative variables. Qualitative variables will be analysed using the chi-squared test (or the Fisher exact test depending on the theoretical number of patients).

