Among novel strategies aimed at treating NAAION, treatment with a systemic endothelin receptor antagonist has recently emerged as a promising new strategy, for the following reasons:NAAION is associated in 75–80% of cases with OSAS [47–49]. The endothelin system is activated in OSAS patients, and endothelin 1 (ET-1) is associated with intermittent hypoxia, a major feature of OSAS [50, 51]. It is also involved in the physiopathology of cardiovascular disease (hypertension, myocardial infarction and/or vascular remodelling, all frequent comorbidities of OSAS).Endothelin 1 is implicated in vascular damage of the optic nerve. In animal models, the application of ET-1 directly to the optic nerve, or in the eyes, induces ischaemic optic neuropathy. An increase in the plasma levels of ET-1 was also found in NAAION patients [52].At the ocular level, bosentan, a duel ET-1 receptor antagonist, increases retinal and optic nerve blood flow in healthy humans and glaucoma patients [53].Bosentan is an already certified medication used in pulmonary arterial hypertension, and for digital ulcers associated with systemic sclerodermia, and has a good tolerance profile. While abnormally high levels of hepatic enzymes occur in approximately 10% of patients, with 3% of them discontinuing treatment, any hepatic toxicity can be easily detected [54].

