### Intervention description {11a}

The treatments are initiated after inclusion and randomisation according to the group to which the patient is assigned: Group 1: oral 125 mg bosentan twice a day (BD) (total dose, 250 mg/day); Group 2: oral placebo, BD. Treatments are administered for 8 weeks.

The coordinating pharmacy prepared the investigational medicinal products (IMP), obtained from Pharmascience Inc. Montréal, Québec. Masking of pms-BOSENTAN 125 mg and 62.5 mg tablets was done by overencapsulation in size #1 opaque capsules. Pms-BOSENTAN 125 mg placebo and pms-BOSENTAN 62.5 mg placebo are empty capsules overencapsulated in the same size #1 and colour opaque capsules. The coordinating pharmacy also performed the packaging and labelling of the IMP and matching placebo. Thus, IMPs and placebos are indistinguishable.

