### Relevant concomitant care permitted or prohibited during the trial {11d}

As far as possible, introducing, or modifying existing, concomitant treatments should be avoided throughout the trial.

The prescription of aspirin at a dosage of between 75 and 300 mg/day is tolerated if it is indicated for cardiovascular disorders in secondary prevention for patients with a history of complicated carotid or coronary atheroma, stroke, arteriopathy of the lower limbs or aneurism of the abdominal aorta. In primary prevention, aspirin will be proposed starting in the 3rd month of the protocol, after discontinuing bosentan or placebo treatment. If necessary, continuous positive airway pressure (CPAP) treatment can be initiated after the visit at 3 months.

Simvastatin treatment requires adapting the dosage to the patient’s lipid profile (cholesterol level), given that bosentan reduces the plasma concentrations of simvastatin. Prohibited treatments or those requiring close monitoring, as well as the related risks, are summarised in Table 4.

**Table 4 Tab4:** Prohibited treatments or those requiring close monitoring

**Prohibited treatments**	**Risks**
Cyclosporine A	Major risk of increasing residual plasma levels of bosentan following transport protein inhibition of bosentan in hepatocytes
	Major risk of decreasing plasma concentrations of cyclosporine with reduction in its efficacy and therefore its immunosuppressive activity
Glibenclamide	Major risk of increasing risk of elevation of liver enzymes
General corticosteroid therapy	Risk of interfering with potential efficacy of bosentan
Amiodarone	Drug giving NAAION-like picture
CYP 3A4- and 2 C9 2C19-inhibitor drugs	Risk of increasing plasma bosentan concentrations
CYP 3A4-, 2C9-inductor drugs	Risk of decreasing plasma bosentan concentrations
Protease- and ritonavir-inhibitor drugs	Risk of increasing plasma bosentan concentrations
Nevirapine	Pronounced hepatotoxicity that can potentially cumulate with that of bosentan.
**Not recommended**	**Close monitoring required**
Anti-coagulants (warfarin and other antivitamin Ks)	INR (3–4 days after beginning of treatment, after each dosage modification and after discontinuation of bosentan treatment) during treatment initiation and/or dosage increase
Hormonal contraceptives (oestrogen/progestin combination and progestin-only pills)	Risk of reducing efficacy

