**Fig. 2 Fig2:**
[figure not shown]
Schedule of enrolment, interventions and assessments for a patient included in the ENDOTHELION trial

Following randomisation, the first administration of the treatment is given in the ophthalmology department. Blood pressure (BP) is checked 4 h after this, corresponding to the plasma peak of bosentan according to the pharmacological data in the study by Weber et al. [59].

Patient monitoring/follow-up includes consultations at week 2, and at 1, 2, 3, 6, 12 and 24 months with one of the investigating ophthalmologists, during which several examinations are carried out: an ophthalmological examination (VA, VF, SD-OCT and fundus examination), a clinical examination searching for the adverse side effects of bosentan, an office-measurement of BP and a blood work-up including a haemogram and measurement of liver enzymes (until and including the month 2 visit). Self-measurement of BP is programmed during weeks 1 and 4 and the last week of treatment (week 8).

The primary endpoint is set at 3 months so as to assess the efficacy of bosentan before initiating treatment for OSAS, the recognised period when visual function usually stabilises, and papillary oedema disappears, proceeding to papillary atrophy. Contreras et al. [60] showed that at 1.5 months following the acute phase, the RNFL thickness of the affected eye was similar to that of the unaffected eye, indicating that the optic disc swelling had partly resolved. After this first period, atrophy of the optic nerve head became detectable, such that at the 3-month visit, the RNFL had thinned by 39%, compared to the contralateral normal eye [60]. Loss of retinal nerve fibre layers stabilised thereafter, with only 6% additional thinning at the 12-month visit. In another study, Hayreh et al. [57] estimated the median time to papillary oedema resolution was 7.9 weeks (IQR, 5.8–11.4 weeks).

In the present trial, at 3 months, the clinical examinations and laboratory analyses (including a study of endothelial function), the ophthalmological examinations (VA, VF, SD-OCT and fundus examination) and the blood work-up (with serum banking) performed at inclusion are repeated. A polysomnography is planned after the 3-month visit.

The visits at 6 and 12 months and the end-of-protocol visit at 24 months include an ophthalmological examination (VA, VF, SD-OCT and fundus examination). The quality-of-life questionnaire (VFQ-25) [58] is completed at the 3- and 12-month visits.

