### Methods in analysis to handle protocol non-adherence and any statistical methods to handle missing data {20c}

All available data will be included in the final mITT analysis, even in case of protocol non-adherence. However, missing data will not be replaced.

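### The second month-3 model chooses covariates by observed imbalance between arms and treats OSAS as baseline, although polysomnography comes after month 3

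*Protocol article*

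**What the plan says.** All references are to the protocol article.

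- **Primary model.** Statistical methods for primary and secondary outcomes {20a} compares the change in visual field mean deviation (MD) from inclusion to month 3 in a linear mixed model with group as a fixed factor and centre as a random effect; "the MD at baseline will be included as a covariate in the model".
- **Second model.** The next paragraph announces a further model of the same kind, "adjusted on the presence of OSAS and on other baseline parameters that potentially differ between the two groups". A parenthesis in that sentence gives its outcome: the Y "variable will be the difference in RNFL: M3 – D1". No candidate list, threshold or selection procedure is given.
- **OSAS timing.** Participant timeline {13}: "A polysomnography is planned after the 3-month visit". Intervention description {11a}: "Treatments are administered for 8 weeks". The section on concomitant care {11d} says that CPAP "treatment can be initiated after the visit at 3 months".
- **Missing values.** Section {20c}: "missing data will not be replaced".

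**The concern.** In a randomised trial, baseline differences between arms are due to chance. A covariate earns its place by predicting the outcome, not by differing between arms. Under the stated rule the model cannot be written down until the arms have been compared, and two competent analysts could reach different models from the same data. A strong predictor that happens to be balanced stays out, and its precision gain is lost.

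The wording also groups OSAS with baseline parameters, while the only assessment described in the text follows both the 8-week treatment and the month-3 outcome. A patient with month-3 data but no polysomnography has no value for this covariate and, without replacement of missing data, drops out of the model.

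Finally, the outcome is unclear. The model sits under the primary endpoint, which is MD, but its stated response is RNFL change. As written, it cannot serve as a check on the MD result.

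**Working it through.** **1. The plan's own figure.** Sample size {14} gives a difference of 6 dB (−15 to −9), SD 9, R² 0.3 for baseline field, alpha 0.05 and power 90%; {20a} makes the tests two-sided.

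- Residual variance = 81 × (1 − 0.3) = 56.7.
- n per group = 2 × (1.960 + 1.282)² × 56.7 / 6² = 33.1, so 34. The t-based version gives 35.
- The plan states 36, where the t-based power is 91.5%. The figure reproduces, and this point does not dispute it.

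**2. How often chance imbalance would change the model.** The number of candidates (K), their independence and the threshold are assumptions, because the plan gives none. P(at least one flagged) = 1 − (1 − threshold)^K.

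| K | p < 0.05 | p < 0.10 |
|---|---|---|
| 8 | 1 − 0.95^8 = 34% | 1 − 0.90^8 = 57% |
| 12 | 1 − 0.95^12 = 46% | 1 − 0.90^12 = 72% |

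In 6,000 simulated trials per scenario (36 per arm, no treatment effect), 8 candidates produced 59 to 67 different covariate sets at p < 0.05 and 112 to 123 at p < 0.10.

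**3. Type I error in the same simulations.** Assumed correlations of each candidate with the outcome were 0.1, 0.2 and 0.27 with 8 candidates, and 0.2 with 12.

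- One fixed threshold (0.05, 0.10 or 0.20): 1.1% to 4.8%, which is conservative.
- Smallest p-value among the model without the candidates and the three threshold rules: 5.7% to 6.8%, against 4.5% to 5.2% for the model without the candidates alone.

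**4. What a balanced predictor is worth.** The share explained is assumed. If it is 10% of residual variance, omitting the predictor costs 1 / (1 − 0.10) = 1.11, or 11% in effective sample size. If it is 10% of total variance beyond the planned 0.3, the factor is 0.7 / 0.6 = 1.17. The trial was powered on baseline field alone, so this is a forgone gain and not a loss of planned power.

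The documents support field-defect type as prognostic for MD. In the retrospective cohort in {14}, inferior altitudinal defects moved from −15.2 to −15.8 dB (0.6 dB worse, n = 14) and superior ones from −14.9 to −17.08 dB (2.18 dB worse, n = 8). The Discussion also reports courses that differ by defect type. The type is recorded at inclusion ({18a}).

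**5. Which baseline value enters.** The plan does not say whether the second model carries baseline MD or baseline RNFL. In one series of 23 affected eyes cited in the Discussion, RNFL was 203.63 ± 81.41 μm acutely and 59.50 ± 11.52 μm from month 3. Whatever the correlation between the two, the SD of the change lies between 81.41 − 11.52 = 69.9 μm and 81.41 + 11.52 = 92.9 μm. Once baseline RNFL is in a linear model, the residual SD is at most 11.52 μm. If that series is any guide, baseline RNFL belongs in an RNFL model whether or not it is balanced.

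**6. Loss through missing polysomnography.** Sample size {14} gives no SD for RNFL, so the MD inputs serve as a proxy. The missing rates among patients with month-3 data are assumed.

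| Polysomnography missing | 72 with month-3 data | 69 with month-3 data (80% of 86) |
|---|---|---|
| 0% | 91.5% power | 90% |
| 10% | 88% | 87% |
| 20% | 84% | 83% |
| 30% | 79% | 77% |

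**The case against.** The strongest reply is that this is a secondary model in a condensed article and that a full covariate list normally belongs in the analysis plan. That is fair as to the list. But the article does more than leave a gap: it states a selection principle, and an analysis plan that followed it would inherit the fault.

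Several stronger readings are tempting, and the documents do not support them.

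- **That the primary result is at risk.** It is not. The primary MD model has group, baseline MD and centre, and nothing in it depends on imbalance or OSAS.
- **That imbalance-led selection inflates false positives.** Applied mechanically, it does not (step 3). Only a free choice among analyses does, and then mildly.
- **That the planned 20% attrition measures the loss of OSAS data.** It does not. That figure covers loss to follow-up and early stopping, including interruptions for side effects. Patients gone before month 3 have no month-3 outcome and leave every month-3 model. The extra loss is confined to those with month-3 data but no polysomnography, for which no rate is given.
- **That bosentan distorts OSAS status through fluid retention.** Table 6 reports oedema or retention in 13.2% against 10.9% on placebo, and no section links this to sleep apnoea. By the time of polysomnography, treatment has been over for weeks. OSAS is chronic and CPAP is deferred until after month 3, so any bias may be small, though it is not excluded.
- **That OSAS explains little because it is so common.** The background states that "NAAION is associated in 75–80% of cases with OSAS". At those values p(1 − p) is 0.19 to 0.16, which is 75% to 64% of the maximum of 0.25, and prevalence does not determine explained variance.

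Figures 1 and 2 were not available for this review, and the Fig. 1 legend lists polysomnography. An earlier recording of OSAS is possible, but no section of the text describes one.

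**Conclusion.** The point holds for the second model only. Its covariate set is fixed by chance imbalance, its outcome is at odds with its placement, and it groups OSAS with baseline parameters although the text describes ascertainment only after month 3. The result is a secondary estimate that is data-driven, less efficient than it could be and not reproducible.

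The direct evidence is the wording. The sizes are illustrative: a 34% to 46% chance of at least one flagged covariate assumes 8 to 12 independent candidates screened at 5%, and a fall in power from 91.5% to 84% assumes 20% missing polysomnography among 72 patients, with MD inputs standing in for RNFL. The OSAS part also rests on Figures 1 and 2 showing no assessment at inclusion.

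**What to change.** Before unblinding:

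1. Delete the rule that selects covariates by difference between arms.
2. State the outcome of the second model: MD change if it is a sensitivity analysis of the primary endpoint, RNFL change if it is a secondary analysis.
3. Pre-specify a short list recorded before randomisation: the baseline value of that outcome, field-defect type collapsed to three or four classes, days from onset to inclusion, and centre as a random effect.
4. Take OSAS out of this model unless status known at inclusion is recorded. Report any model adjusted for the later polysomnography as exploratory, with the number of patients excluded by arm. The later result remains usable for the comparison by OSAS treatment after month 3 planned in {20b}.

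**Cost.** This is a wording change and needs no new data. Four defect classes use 3 degrees of freedom and days from onset uses 1, so 4 in all against about 72 patients. The 11 defect types listed in {18a} would use 10 uncollapsed, which is why they should be grouped. The sample size does not change.

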### Sample size {14}

The sample size calculation was based on VF data (primary outcome) from a published study [61], and from a retrospective analysis of the patient cohort at Grenoble-Alpes University Hospital (personal data). Bellusci et al. [61] showed that inferior VF defects varied from −11.7 ± 2.7 at diagnosis to 10.3 ± 3 dB (*n* = 5) at 6 months, with diffuse defects varying from −15.5 ± 7.4 to −16.4 ± 7.9 dB (*n* = 7) and central defects varying from −5.3 ± 0.7 to 4.8 ± 1.7 dB over the same timespan (*n* = 4). Consistently, in our retrospective cohort, the progression of inferior altitudinal VF defects (*n* = 14) showed an 11% deterioration in the mean deviation (MD) between 3 and 6 months (from −15.2 ± 9 initially to −15.8 ± 7.8 dB) and 21% worsening of the MD for superior altitudinal defects (*n* = 8, from −14.9 ± 4.2 dB initially to −17.08 ± 5.7 dB).

We hypothesised that the mean deviation at inclusion would be −15 ± 9 dB and that the treatment would provide a 40% improvement in the defect, i.e. a progression from −15 to −9 dB, while no change is expected in the placebo arm. A sample size of 36 patients per group would thus provide 90% power to detect such a difference using a general linear model, with a common standard deviation of 9, an alpha risk of 0.05 and with an *r*-squared for the covariate (VF at baseline) of 0.3. To take account of patients lost to follow-up and/or those with prematurely stopping the protocol (including interruptions related to the side effects of bosentan, evaluated at 20% of the sample, *n* = 14), a total of 86 patients need to be included (*n* = 43 per group).

This sample size should provide >90% power to detect a significant difference in the thinning of retinal nerve fibres, hypothesising a smaller reduction in RNFL thickness after treatment (reduction evaluated at −43% in the placebo arm patients versus −25% in patients treated with bosentan), using an ANCOVA.

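### The log-transform fallback is undefined for mean deviation and for change scores, and it is triggered by the variables' distributions, not by model residuals

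*Protocol article*

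**What the plan says.** All of the analysis text is in the protocol article, under Statistical methods for primary and secondary outcomes {20a}.

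- **Primary response:** the change in MD, "i.e. delta M3 – D1, will be compared between the two groups using a linear mixed effects model". Group is a fixed factor and centre a random effect.
- **Covariate:** "the MD at baseline will be included as a covariate in the model".
- **Second model:** of the same type, adjusted for sleep apnoea and other baseline factors. Its response is given in a bracket: the "variable will be the difference in RNFL: M3 – D1".
- **Visual acuity:** analysed in the same way as the primary endpoint.
- **Normality check:** "Data normality will be evaluated graphically and tested using the Shapiro-Wilk test".
- **Action if not normal:** "The quantitative variables will be log-transformed if their distribution is not normal, so as to satisfy the conditions required to apply linear models". This sentence comes directly after the description of the second model.

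A rank test is offered as an alternative only for the remaining secondary comparisons, not for the linear models. No offset, reflection or other device is given for values that are zero or negative.

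Under Sample size {14}, the planning values are: "We hypothesised that the mean deviation at inclusion would be −15 ± 9 dB", with bosentan giving "i.e. a progression from −15 to −9 dB, while no change is expected in the placebo arm".

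**The concern.** The variables that the section puts into linear models are baseline MD, change in MD, change in retinal nerve fibre layer (RNFL) thickness and change in visual acuity. The first is a negative dB value in nearly every affected eye. The others are differences that can be negative. The one remedy that the plan states for non-normality therefore cannot be applied to these variables as written.

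The trigger is also misplaced. A linear model asks for roughly normal residuals. It does not ask that the response or a covariate be normal on its own, and baseline MD can be skewed without harm to the model.

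If the fallback were invoked for the primary endpoint, someone would have to invent a shift, a sign change or another method with the data in view. The treatment effect would then no longer be a difference in dB. It could not be read against the 6 dB planning effect or against the 2 dB minimum significant change given under Plans for assessment and collection of outcomes {18a}.

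**Working it through.** **1. The planning inputs reproduce.** The inputs from Sample size {14} are a difference of 6 dB (−15 to −9), SD 9, r² = 0.3 for baseline, alpha 0.05 and 90% power. The test is two-sided, from {20a}.

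- Residual SD = 9 × √(1 − 0.3) = 7.53 dB.
- n per group = 2 × [7.53 × (1.960 + 1.282) / 6]² = 33.1, so 34. A noncentral t calculation gives 35.
- The protocol states 36, which is close enough to use its inputs below.

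**2. Baseline MD.** With mean −15 and SD 9, and a normal distribution assumed:

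- P(MD < 0) = Φ(15/9) = Φ(1.67) = 0.952.

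**3. Change in MD.** The protocol gives no SD for the change. I assume SD 9 at both visits and take the correlation as √0.3 = 0.548.

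- SD of change = 9 × √[2 × (1 − 0.548)] = 8.56 dB.
- Placebo, mean change 0: P(change ≤ 0) = 50.0%.
- Bosentan, mean change +6: P(change ≤ 0) = Φ(−6/8.56) = 24.2%.
- Overall: (50.0 + 24.2) / 2 = 37.1%, or about 27 of 72 evaluable patients and 32 of 86 randomised patients.

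The SD of change is an assumption, so its range matters:

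| SD of change (dB) | Placebo ≤ 0 | Bosentan ≤ 0 | Overall |
|---|---|---|---|
| 3 | 50% | 2.3% | 26% |
| 5 | 50% | 11.5% | 31% |
| 8.56 | 50% | 24.2% | 37% |
| 9 | 50% | 25.2% | 38% |

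The Discussion supports mixed signs. In one cited prospective series of 27 patients, MD worsened by at least 2 dB in 29.6% and improved by at least 2 dB in 48.2%.

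**4. Change in RNFL.** The Discussion cites a series with 203.63 ± 81.41 µm in the acute phase and 59.50 ± 11.52 µm from month 3.

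- Mean change = 59.50 − 203.63 = −144.13 µm.
- SD of change = √(81.41² + 11.52² − 2r × 81.41 × 11.52), which is 82.2 for r = 0 and 75.1 for r = 0.6 (r assumed).
- P(change < 0) = Φ(144.13/82.2) = 96.0%, up to Φ(144.13/75.1) = 97.3%.

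**5. What an improvised repair does.** This is one simulated data set with assumed skew (72 patients, 36 changes at or below zero). It is an illustration and not an estimate for this trial. The untransformed model gave p = 0.006. The shifted log of (change − minimum + c) gave:

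| c | Treatment p | Shapiro-Wilk p after transformation |
|---|---|---|
| 0.1 | 0.0004 | < 0.001 |
| 1 | 0.00015 | 0.007 |
| 5 | 0.0003 | 0.26 |
| 20 | 0.0013 | 0.0015 |

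Dropping the 36 non-positive values and logging the rest gave p = 0.27. Only one of the four shifts passed the normality test, so an analyst aiming for normality would have to tune the constant to the data.

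**The case against.** The strongest reply is that the primary analysis is fully specified and can be run. The paragraph that defines it contains no transformation. The log sentence stands in the next paragraph, after the RNFL model, and may have been meant for that model only. RNFL thickness is positive at both visits, so it could be logged before differencing. That would suit the percentage reductions in RNFL assumed under Sample size {14}. The rule is also conditional, and graphical assessment is named beside Shapiro-Wilk, so no automatic switch is stated. In the illustration, every shift led to the same conclusion as the untransformed model.

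Much of this stands, and it rules out several stronger readings.

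- A reader might infer that the primary analysis cannot be executed. The documents do not support this: the dB-scale model runs unless non-normality is declared and acted on.
- A reader might infer that the rule fails for nearly every patient. That describes baseline MD and RNFL change. For the primary response the share is about 37%, because change in MD has mixed sign.
- A reader might infer that MD is piled up at a floor, so that Shapiro-Wilk will reject. The protocol gives no floor and no distribution for the change, so the chance that the fallback is invoked is unknown.
- A reader might infer that patients with undefined logs would be dropped. The protocol does not say so, and {20c} says that all available data are to be included.

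What does not stand is the claim that only a detail is missing. The sentence speaks of quantitative variables and linear models in general, and one value at or below zero is enough to make a plain log undefined. On the narrow reading, the response that the text names is still a difference; logging thickness first is a sensible repair, but it is not what is written. An analysis plan that followed this sentence would carry the fault forward.

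**Conclusion.** The point holds for the conditional fallback, and the severity is should-fix. As worded, the rule cannot be applied to baseline MD (about 95% negative), to change in MD (about 37% at or below zero, range 26% to 38%) or to the RNFL difference (about 96% to 97% negative). Its trigger looks at the distributions of the variables when model residuals are what matter.

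These shares rest on normal distributions and on the protocol's planning values. For the change in MD they also rest on an assumed SD of change, and for RNFL on one cited series and an assumed correlation. The conclusion does not depend on the exact shares, since some non-positive values are certain under any of them.

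The sample size, the primary endpoint and the main model are unaffected. What is at stake is a choice of scale for the primary result that could be made after the data are seen.

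**What to change.** Replace the log-transform sentence with wording to this effect:

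- MD, visual acuity and all change scores are analysed on their original scale, whatever the Shapiro-Wilk result.
- Model assumptions are judged on the residuals of the fitted model, mainly by graphs.
- Log transformation is limited to strictly positive variables, such as laboratory markers. RNFL thickness may be logged before differencing if a ratio is the effect wanted.
- If residuals are clearly non-normal, the dB-scale estimate stays primary and is supported by one sensitivity analysis named in advance. A bootstrap interval or a rank-based analysis of covariance would do; the choice matters less than fixing it before unblinding.

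The cost is one paragraph in the protocol or analysis plan. No new data, no extra patients and no change to the primary model are needed.

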### Outcomes {12}

The *primary endpoint* (a) is the mean deviation in VF (in dB) 3 months after inclusion. This endpoint is considered sufficient to assess functional and anatomic recovery with the disappearance of optic disc swelling by this time [57].

The *secondary endpoints* are as follows: (b) peripapillary retinal nerve fibre thickness (RNFL) and macular ganglion cell layer thickness measured using SD-OCT at 3, 6, 12 and 24 months after inclusion; (c) visual function (VA using the ETDRS scale and VF) at 6, 12 and 24 months: (d) the extent of bilateralisation of NAAION at 24 months; and (e) quality-of-life parameters assessed using the visual function questionnaire (VFQ-25) [58] at 3 and 12 months.

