## Assignment of interventions: allocation

### Sequence generation {16a}

Centralised randomisation with computer-generated random numbers, stratified by study centre, is used to randomly assign patients who meet the inclusion criteria to the bosentan or the placebo group. A MEDSHARING IWRS (Interactive Web Response System) server is used for randomisation.

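### MD after month 3, later RNFL and ganglion-cell thickness are, as written, compared without baseline covariate or centre, although MD at month 3 and VA are adjusted for both

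*Protocol article*

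**What the plan says.** All references are to the protocol article.

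- **Primary endpoint, section {20a}.** The month-3 minus baseline change in MD is compared in a linear mixed model with group as a fixed factor and centre as a random effect, and "the MD at baseline will be included as a covariate in the model".
- **Secondary endpoints, section {20a}.** For these, "the same type of analysis as that used for the primary endpoint will be used for VA". Then: "Other comparisons between the two groups will be made using the Student" t test or the Mann–Whitney U test, chosen by normality, for quantitative variables. Chi-squared or Fisher tests serve qualitative ones.
- **Outcomes {12}.** Endpoint (b) is RNFL and macular ganglion-cell thickness at 3, 6, 12 and 24 months. Endpoint (c) is visual function, given as "VA using the ETDRS scale and VF) at 6, 12 and 24 months".
- **RNFL at month 3, section {20a}.** A second model of the primary type is adjusted for OSAS and for baseline parameters that differ between groups. A parenthesis adds that its Y "variable will be the difference in RNFL: M3 – D1".
- **Sample size {14}.** The MD calculation takes an R-squared "for the covariate (VF at baseline) of 0.3". The RNFL power statement ends "versus −25% in patients treated with bosentan), using an ANCOVA".
- **Sequence generation {16a}.** Randomisation is "stratified by study centre".

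**The concern.** VA is the only secondary endpoint that the secondary-endpoint paragraph assigns by name to the primary-type model. Everything else quantitative falls to the two-sample tests. The same MD measurement is therefore adjusted for baseline and centre at month 3 and, as written, for neither from month 6, while VA, listed beside it in endpoint (c), keeps the adjustment. No reason is given.

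For RNFL, the sample size section relies on an ANCOVA, and section {20a} gives an adjusted model for the month-3 change only. Nothing carries it to 6, 12 and 24 months.

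At stake is precision on the functional and structural endpoints after month 3, in a trial sized at 36 evaluable patients per arm. Where the Mann–Whitney test is chosen, the test itself also yields no difference in dB or μm. The baseline values and the centre are already held, so the loss is avoidable.

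**Working it through.** **1. Which analysis each endpoint gets, read literally**

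| Endpoint | Analysis in {20a} |
|---|---|
| MD, month 3 (primary) | Mixed model: baseline covariate, centre |
| VA | Same type of model |
| RNFL, month 3 | Second model of the same type (in a parenthesis) |
| MD, months 6, 12, 24 | t or Mann–Whitney |
| Ganglion-cell thickness, all visits | t or Mann–Whitney |
| RNFL, months 6, 12, 24 | t or Mann–Whitney |

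**2. Inputs for MD, from Sample size {14}**

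Difference 6 dB (−15 to −9 dB against no change), common SD 9 dB, R-squared 0.3, alpha 0.05 (two-sided per {20a}), 36 per arm.

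**3. Reproducing the plan's figure**

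- Adjusted residual SD = 9 × √(1 − 0.3) = 7.53 dB.
- n per arm = 2 × (1.960 + 1.282)² × 7.53² / 6² ≈ 33.1, so 34 by the normal approximation and 35 by the noncentral t.
- Power at 36 per arm by the noncentral t: 91.5%.

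The stated 36 per arm for 90% power is reproduced to within two patients, but only with baseline adjustment.

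**4. The same inputs without the covariate**

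The change-score row assumes equal SDs at both visits and correlation √0.3 = 0.548. The SD of change is then 9 × √(2 × (1 − 0.548)) = 8.56 dB.

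| Test | SD (dB) | Power, 36 per arm | n per arm for 90% | Variance ratio to adjusted |
|---|---|---|---|---|
| Baseline-adjusted | 7.53 | 91.5% | 35 | 1 |
| t on change | 8.56 | 83.5% | 44 | 0.905 / 0.70 = 1.29 |
| t on visit value | 9.00 | 79.7% | 49 | 1 / 0.70 = 1.43 |

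The variance ratios mean about 29% and 43% more patients for the same precision.

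**5. Sensitivity to R-squared**

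The documents give no R-squared for later visits, so it is varied as an assumption.

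| Assumed R-squared | Adjusted | t on change | t on visit value |
|---|---|---|---|
| 0.1 | 83.6% | 66.5% | 79.7% |
| 0.3 | 91.5% | 83.5% | 79.7% |
| 0.5 | 97.6% | 95.4% | 79.7% |

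The adjusted model has the highest power in every row. The effect of omitting centre is not quantified, because no between-centre variance is given.

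**6. RNFL is a separate case**

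The Discussion quotes a published series with mean RNFL 203.63 ± 81.41 μm in the acute phase and 59.50 ± 11.52 μm from month 3 to month 12. If those SDs applied here, with correlation r assumed between 0 and 1:

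- SD of change = √(81.41² + 11.52² − 2 × r × 81.41 × 11.52), which is 82.2 μm at r = 0 and 69.9 μm at r = 1.
- Residual SD after adjusting for baseline = 11.52 × √(1 − r²), which is at most 11.52 μm.

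An unadjusted test on RNFL change would thus be dominated by variation in acute swelling. How far baseline RNFL predicts the later value is unknown, so the gain over a test on visit values cannot be stated.

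**The case against.** The strongest reply is that unadjusted tests are valid in a randomised trial. For mean differences, the unadjusted and the linear baseline-adjusted comparisons estimate the same quantity and differ only in precision. That stands: a reader might infer bias, or estimates that cannot be compared over time, and the documents support neither.

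Other stronger readings also fail:

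- **That every secondary endpoint loses precision.** VA and month-3 RNFL have adjusted models, and bilateralisation is a binary event. The readable text places VFQ-25 at 3 and 12 months only, but the schedule figure is not shown, so nothing firm can be said about its baseline.
- **That the RNFL ANCOVA is contradicted outright.** The month-3 model is covariate-adjusted. The gap is confined to later visits and to where that model is placed in the text.
- **That the baseline is discarded.** Section {20a} does not say whether values or changes are tested, and the Abstract describes these outcomes as changes. A test on change uses the baseline, though inefficiently. For MD the 29% figure then applies, not 43%. Centre is omitted either way.

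Section {20b} does plan a mixed model with centre as a random effect and interactions involving group. It is an additional analysis of OSAS treatment that stops at 12 months, so it does not replace the secondary between-group comparison.

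Finally, a condensed article may leave visit-level models to an analysis plan. Here, however, the article does not stay silent: it names a test, and that test is the weaker one.

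**Conclusion.** The point holds for MD at 6, 12 and 24 months, ganglion-cell thickness at all visits and RNFL at 6 to 24 months. It concerns efficiency and consistency in secondary analyses only.

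For MD, the cost is about 8 points of power if changes are tested (91.5% to 83.5%) and about 12 points if visit values are tested (91.5% to 79.7%). This rests on carrying the month-3 effect, SD, R-squared and 36 per arm to later visits, and for changes also on equal SDs and correlation √0.3. These ratios do not transfer to RNFL or ganglion-cell thickness. For RNFL only the direction is clear: an unadjusted test on change is a poor choice because acute swelling drives its variance.

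**What to change.** In section {20a}, state that MD, RNFL and ganglion-cell thickness at every secondary visit are analysed with the primary-type linear mixed model, with the endpoint's own baseline value as covariate and centre as random effect, reporting the adjusted difference and 95% CI at each visit. Move the RNFL model out of its parenthesis, and reconcile the RNFL analysis at each visit with the ANCOVA named in section {14}. Keep the two-sample tests for quantitative variables without a baseline value.

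A single repeated-measures model across visits, and baseline covariates for VFQ-25, are optional refinements. The cost is a few sentences and some programming, with no added data collection. The change should be dated before unblinding.
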